## **2.5 Study procedures**

Women treated for GDM 5 years previously will identified from the existing registers, who fit the inclusion criteria will be contacted and invited to participate. Those who verbally agree to participate will be advised about the OGTT and the fasting requirements. The participation

will be roughly two and a half hours. Upon arrival at the study site, the study will be explained to the participants and they will be requested to sign a written informed consent. Once this is signed they will undergo the study procedures: blood samples for an HbA1c test, a 2-hour OGTT, a 30 – 45-minute interviewer will administer the questionnaire, anthropometry and blood pressure will be measured. A medical chart review will be undertaken for each participant after they have finished the OGTT and questionnaire.

## **2.6 Medical chart review**

Clinical data pertinent to the index pregnancy will be collected via a review of the individual patient hospital records, using a structured data collection form. Data collected will include: maternal age gestational age and OGTT result at time of GDM diagnosis, insulin and oral hypoglycemic agent use during GDM, BMI at booking, infant birthweight (macrosomia or not – using birthweight of 4000g as cut off), and outcome of pregnancy (stillbirth and fetal complications), parity, previous GDM, and comorbidities such as pre-eclampsia, lipid levels if measured and diabetes therapy at time of discharge.

## **2.7 Questionnaire**

The questionnaire will have:

- Demographic data section– data on age, level of education, marital status, area of residence, employment status and ethnicity. Ethnicity will be self-reported and care will be taken to include an “other” option for ethnicity to accommodate participants who may not be comfortable in disclose their ethnicity.
- Medical history – data on comorbidities e.g. hypertension, post GDM pregnancy breastfeeding, family history of Type 2DM, parity, self-reported postnatal DM followup and current medications including anti-retroviral therapy.
- Other variables – data on smoking history, alcohol use history, psychosocial health, diet and physical activity will be assessed using established methods (4).

## **2.8 Anthropometry and blood pressure**

Height, weight, and waist and hip circumferences will be measured using standardized techniques (34).

## **2.9 Oral Glucose Tolerance Test and HbA1c**

Participants will be given 75g anhydrous glucose in 250ml of water, in the morning after a 10-12 hour overnight fasting period (3). Venous blood samples will be taken at 0 minutes for glucose, lipogram and for HbA1c measurement, at 30 minutes and 120 minutes for glucose

and insulin. The bloods will be kept on ice, and sent to the laboratory for handling and measurement of the same day using commercially available test kits. T2DM will be diagnosed according to WHO guidelines (3). One additional blood sample (5ml each) will be taken from each participant, centrifuged and the serum stored in case some samples get spoiled or if confirmation is needed or an additional investigation relating to GDM is considered. The samples will be stored up to 5 years after the study and thereafter destroyed. Ethics approval will be sought if any additional investigations are performed. Any participants who are already on treatment for T2DM will not be required to do either the OGTT or the HbA1c.

## **2.11 Sample Size**

Sample size for evaluating the prevalence of postnatal T2DM was calculated using the formula

$$\frac{p(1-p)z^2}{d^2}$$

With  $p$  = the hypothesized proportion of GDM women who have postnatal T2DM,  $z = 1.96$  (corresponding to a 0.05 level of significance) and  $d$  = the precision to which the prevalence is to be estimated.

Most studies found a prevalence of T2DM during the first 5 years after GDM diagnosis between 20% and 50% (14).

The total number of women treated for GDM at the hospital during the period 1 September 2010 to 31 August 2011 was 498. Using 498 as the total population, a hypothesized prevalence of 40% and aiming to estimate the prevalence of T2DM to within 5 percentage points ( $d = 0.05$ ), the study would require a sample size of 213.

Since the population is finite, we will endeavor to recruit all the 498 women, however, conservatively estimate that the study will be able to recruit 50% of these women, as our population is highly mobile and, apart from loss to follow-up and relocation, contact details in the hospital registers are not very accurate and some change their contact details.

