## **1.2 Rationale and Motivation**

Although evidence from systematic reviews suggests that GDM is a risk factor for T2DM, the extent of this risk is not known in Africa nor are the factors associated with the risk of development of T2DM. The T2DM disease burden in this high-risk population is not known in sub-Saharan Africa. The factors that may increase the risk of T2DM development in this vulnerable group may differ to those identified in high income countries. Any future interventions for the prevention of T2DM in women with a history of GDM need to be informed by evidence which is specific to the African context.

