### **1.2 Aim and Objectives**

The aim of the study is to determine the prevalence of and risk factors for T2DM in women who had GDM 5 years previously, in South Africa.

The aim will be achieved by the following objectives;

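### The printed sample-size formula gives 369, not 213; the 213 and its ±5 points rest on an unprinted finite-population correction and apply only to the 498 register women, not to the wider aim

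*Protocol*

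**What the plan says.** Protocol section 2.11 opens with "Sample size for evaluating the prevalence of postnatal T2DM was calculated using the formula" and displays p(1-p)z²/d². It sets z = 1.96, "corresponding to a 0.05 level of significance", and defines d as the precision of the prevalence estimate. The displayed formula has no population-size term.

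The section counts 498 women treated for gestational diabetes (GDM) at the hospital between 1 September 2010 and 31 August 2011. It continues "Using 498 as the total population, a hypothesized prevalence of 40% and aiming to estimate the prevalence of T2DM to within 5 percentage points" and concludes that "the study would require a sample size of 213". It then calls the population finite, says the team will try to recruit all 498, and expects to reach half of them.

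The section headed Aim and Objectives sets the target more widely: the prevalence of and "risk factors for T2DM in women who had GDM 5 years previously, in South Africa". The section headed Rationale and Motivation adds that future interventions "need to be informed by evidence which is specific to the African context".

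**The concern.** Two things do not fit together.

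- **Formula and result.** A reader who applies the printed formula to the printed inputs does not get the printed answer.
- **Population.** The step that closes the gap treats 498 women at one hospital as everyone of interest. It removes the uncertainty that would remain if those women were seen as a sample of a larger group. The aim refers to such a larger group.

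This is the only precision statement in the protocol, and it serves the first objective. If the ±5 points is read as the precision for South African women with previous GDM, it is too favourable.

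**Working it through.** **Inputs, all from section 2.11:** p = 0.40, z = 1.96, d = 0.05, N = 498, and expected recruitment 50% × 498 = 249.

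**1. The printed formula**

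n₀ = p(1-p)z²/d² = 0.40 × 0.60 × 1.96² / 0.05² = 368.8, rounded up to 369. This is not 213.

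**2. Reproducing the plan's figure**

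With the usual finite-population correction:

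n = n₀ / (1 + (n₀ - 1)/N) = 368.8 / (1 + 367.8/498) = 212.1, rounded up to **213**.

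The simpler variant n₀/(1 + n₀/N) gives 211.9, that is 212. The first form reproduces the stated number.

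**3. Precision with and without the correction**

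Half-width without the correction: h = 1.96 × √(0.24/n). With it: h × √((498 - n)/497).

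| n | Without correction | With correction (498 women only) |
|---|---|---|
| 213 | 6.58 points | 6.58 × √(285/497) = 4.98 points |
| 249 (expected) | 6.09 points | 6.09 × √(249/497) = 4.31 points |

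**4. Sensitivity to prevalence**

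Section 2.11 cites a range of 20% to 50% from other studies. Over that range:

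- At n = 249 the half-width is 5.0 to 6.2 points without the correction and 3.5 to 4.4 with it.
- At n = 213 it is 5.4 to 6.7 points without and 4.1 to 5.1 with it.

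**5. Sensitivity to the population size**

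The 498 cover 12 months, while section 2.3.1 admits women diagnosed and treated in 2010–2011. The protocol does not give the count for that longer period. Suppose, purely for illustration, that it were twice as large (N = 996). The corrected size would be 368.8/(1 + 367.8/996) = 269.3, that is 270. At n = 213 the corrected half-width would be 6.58 × √(783/995) = 5.8 points. The corrected figure thus depends on which register is meant; the uncorrected one does not.

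**The case against.** The best defence is that 213 is a correct number with its basis disclosed. It comes exactly from a standard correction, and the text names 498 as the total and says the population is finite. For prevalence among those 498 women, under random sampling, ±5.0 points at 213 is right. This stands: a reader might infer an arithmetic slip or a concealed step from 369 against 213, and the protocol supports neither. The display simply lacks the correction.

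A second defence is that the target is narrower than the aim sounds. The numbered objectives do not mention South Africa, sections 2.2 and 2.3 confine the study to one hospital, and the country name could mark the location. The rationale text explains why the study is wanted; it does not define what is estimated. This has some force, but the aim as worded reads more widely than the 498, and nothing in section 2.11 tells the reader that its precision is limited to them.

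Third, the uncorrected figures carry an assumption of their own. A reader might infer that 369 women would secure ±5 points nationally, or that a ±5 interval has some calculable coverage for South African women. Either would need a simple random sample of that wider group. Section 2.3 describes women from one hospital who can be traced, with most contact numbers obsolete. Hence neither claim is made here.

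Finally, nothing shows that intervals that are too narrow will be reported. Section 2.13.2 promises 95% intervals and a prevalence that takes account of the sample design and the realized sample, without saying whether a correction applies. That detail may properly sit in a statistical analysis plan, and its absence is not held against the protocol.

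**Conclusion.** The point holds in a limited form. The formula in section 2.11 gives 369 and needs the omitted finite-population correction to give 213. The ±5 points then applies to the 498 register women, assuming a random sample of them, while the aim is stated for South Africa.

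For inference beyond the register at 40% prevalence, the half-width is about ±6.1 points at the expected 249 participants and ±6.6 at 213. At 249 the corrected half-width (±4.3) is about 29% narrower than the uncorrected one (4.31/6.09 = 0.71). All these figures describe sampling error alone. Selection through one hospital, tracing and consent is not in them, and dropping the correction does not deal with it.

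The importance is moderate. Because the plan already tries to recruit all 498 women, 213 is not a stopping target, and correcting the statement changes nobody's recruitment. What changes is the precision the study can claim.

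**What to change.** Keep the recruitment plan and amend section 2.11 as follows:

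- Print the formula actually used, n = n₀/(1 + (n₀ - 1)/N) with n₀ = p(1-p)z²/d² and N = 498, and show n₀ = 369 as the intermediate step.
- Label 213 and ±5 points (±4.3 at 249) as applying only to prevalence among the 498 register women, assuming a random sample of them.
- For the stated aim, write for example: *With the expected 249 participants, the 95% confidence interval half-width at 40% prevalence is ±6.1 percentage points (±6.6 at 213). This reflects sampling error only.*
- State that prevalence confidence intervals used for conclusions beyond the register are computed without the correction.
- Reconcile the 12-month count of 498 with the 2010–2011 eligibility period, since N drives the corrected figure.

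The cost is a few sentences and a less favourable stated precision. Recruitment and procedures do not change.

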## **2.13 Data management and analysis**

### **2.13.1 Data capturing**

All data will be captured on a pre-coded Microsoft Office Access Database (Microsoft Corporation, 2013) by trained research assistants. Double data entry will be used. All data will be de-identified before capturing by using assigned participant study identities. Signed informed consent forms and questionnaires will be kept in secure locked cabinets.

### **2.13.2 Statistical data analysis**

All statistical analysis will be carried out using Stata 14 (37). For all analysis, the level of significance will be set at 0.05, 2-sided p-values and 95% Confidence Interval (95% CIs) will be reported. Crude T2DM prevalence will be calculated taking into consideration the sample design and the realized sample (4). For categorical variables frequencies and proportions will be reported, while bar graphs and pie chart will be used to present data where appropriate. The chi squared test, Fischer's Exact (small frequencies) and McNemar's chi squared Test (paired data) will be used to compare categories.

All continuous data will be tested for Normality using the Shapiro Wilks test and histogram plots. Means and standard deviations will be presented for variables that are normally distributed while medians and IQRs will be reported for variables that do not follow the Normal Distribution. Box and whisker plots, histograms, scatter plots and line graphs will be used to present data where appropriate. The t-tests and ANOVA (more than two groups) will be used to test to compare continuous outcomes between groups if data are normally distributed. For data that are not normally distributed, comparisons will be tested using Mann U Whitney, Wilcoxon sum rank (2 independent groups), Wilcoxon rank tests (paired data) as well as the Kruskal-Wallis for more than two groups.

Multivariate logistic regression, will be used to evaluate risk factors. Odds Ratios (ORs), their 95% CIs and p-values will be reported. Variables with p-values below 0.1 in the univariate analysis will be considered for the multivariate logistic regression. Additional analysis will include subgroup analysis for different ethnicities, should ethnicity prove to be an independent predictor of risk of T2DM.

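### Making ethnic subgroup analysis conditional on a main effect of ethnicity is the wrong trigger if the aim is to see whether risk-factor associations differ by ethnicity

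*Protocol*

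**What the plan says.** Section 2.13.2 of the protocol sets the test level for all analyses: "the level of significance will be set at 0.05, 2-sided p-values". For objective 2 it says: "Multivariate logistic regression, will be used to evaluate risk factors". Entry to that model is screened: "Variables with p-values below 0.1 in the univariate analysis will be considered for the multivariate logistic regression". The closing sentence of the section then reads: "Additional analysis will include subgroup analysis for different ethnicities, should ethnicity prove to be an independent predictor of risk of T2DM".

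The section does not say what is to be estimated within ethnic groups, and it mentions no ethnicity-by-factor interaction. Section 2.7 makes ethnicity self-reported with an open category, and gives neither the number nor the expected size of the groups. Section 2.11 sizes the study for overall prevalence only: "a hypothesized prevalence of 40% and aiming to estimate the prevalence of T2DM to within 5 percentage points".

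**The concern.** In a logistic model, the ethnicity coefficient describes how the odds of T2DM differ between groups with the other factors held fixed. The ethnicity-by-factor product term describes how the odds ratio of that factor differs between groups. They are separate parameters. A rule that looks at the first before deciding whether to examine the second can close when associations do differ, and can open when they do not.

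At stake is part of objective 2. If a factor matters in one ethnic group and not in another, the overall odds ratio averages over the two, and the planned rule may mean that nobody looks. If the screen at p < 0.1 applies to ethnicity as to any other variable, ethnicity must pass that as well before it can count as an independent predictor, which can only narrow the trigger.

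If the sentence means only T2DM prevalence by ethnicity, the problem is different and milder: estimates would appear when the groups differ significantly and be left out when they do not.

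**Working it through.** **1. The plan's own figure.** Inputs from section 2.11: p = 0.40, d = 0.05, z = 1.96, N = 498.

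- n0 = p(1 − p)z²/d² = 0.24 × 3.8416 / 0.0025 = 368.8
- With finite-population correction: 368.8 / (1 + 367.8/498) = 212.1, rounded up to 213.

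This agrees with "the study would require a sample size of 213". Expected recruitment is 50% of 498 = 249. Both sizes are used below.

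**2. Assumptions, since the protocol gives none.** Two ethnic groups, the smaller holding 50% or 30% of the women; one binary risk factor present in half of them; a true odds ratio of 1 in one group and 4 in the other. The trigger is taken as a two-sided Wald test at 0.05 of ethnicity, adjusted for the factor. Frequencies come from simulation, with about 3,000 or more runs per setting.

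**3. Real difference, baseline odds fully offsetting it** (T2DM prevalence 40% in both groups). In the second group this needs a prevalence of about 24% in unexposed and 56% in exposed women, which averages 40%.

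| | n = 213 | n = 249 |
|---|---|---|
| Condition met | 4–6% | about 5% |
| Interaction test significant, if run regardless | 59–68% | 66–74% |

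The condition is met at about its false-positive rate, so the analysis is suppressed in about 95% of studies.

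**4. The same difference, baseline odds not offsetting it** (30% prevalence in unexposed women of both groups). A hand check with equal groups at n = 213:

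- Group with OR 1: prevalence 30%, odds 0.30/0.70 = 0.4286.
- Group with OR 4: exposed odds 4 × 0.4286 = 1.714, so 63.2% of exposed women; group prevalence (30% + 63.2%)/2 = 46.6%.
- Crude ethnicity odds ratio: (0.466/0.534)/0.4286 = 2.03; log = 0.710.
- SE = √[1/(106.5 × 0.30 × 0.70) + 1/(106.5 × 0.466 × 0.534)] = 0.287.
- Probability of meeting the condition: Φ(0.710/0.287 − 1.96) = Φ(0.51) ≈ 0.70.

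The adjusted simulation gives about 71% for this layout, and 64–71% at n = 213 and 71–79% at n = 249 over both group splits. Suppression therefore runs from 1 − 0.79 = 21% to 1 − 0.64 = 36%.

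**5. No difference in association, but a main effect** (prevalence 30% versus 50%, common odds ratio 2). The condition is met in 79–91% of studies, while the interaction test stays at 4–6%. Meeting the condition is thus no sign that associations differ.

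**The case against.** The strongest reply is that the protocol never says what the subgroup analysis estimates. If it is a description of T2DM prevalence by ethnicity, a main effect is a natural trigger, and the general provisions of section 2.13.2 (proportions, chi-squared comparisons, 95% CIs) already supply much of it. This stands as a limit: the point depends on a reading that the sentence's position favours but does not settle. Even on the other reading, tying the display to significance remains selective.

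It is also fair to restrain an unpowered additional analysis. With four equal groups of about 62 women (249/4, assumed), a simulated 3-df interaction test has only about 13% power for odds ratios 2, 2, 2, 4; 16% for 1, 1, 2, 2; and 47% for 1, 1, 1, 4. That is a reason to keep the list of factors short and label it exploratory. It does not make a main effect a sensible filter.

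Three stronger inferences are tempting and should not be drawn:

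- *That spurious ethnic differences will be reported.* The protocol does not say that significance will be compared across groups, and an interaction test could properly be placed in an SAP. In the four-group layout with a common odds ratio of 2, 40% prevalence and a balanced factor, each group has 27% power (SE = √(4/(62 × 0.24)) = 0.518), and the groups disagree on significance with probability 1 − 0.267⁴ − 0.733⁴ = 0.71. That follows from small groups, however, and would occur without the condition too.
- *That the rule defeats the study's rationale.* The remarks on a possibly different genotype (Abstract and section 1.1.1) contrast the sub-Saharan region with high-income countries. They do not contrast ethnic groups within this cohort.
- *That a real difference would be missed 95% of the time.* That is the extreme case in which baseline odds cancel the interaction.

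**Conclusion.** The point holds in a limited form. The condition is fixed in the protocol text, so an SAP that follows it would inherit it. As a screen for differing risk-factor associations it tests the wrong parameter, and that conclusion needs no assumed figure. Its size does: with two groups, a balanced binary factor and odds ratios of 1 versus 4, suppression ranges from roughly 21% to 95%. A contrast of 1 versus 4 is large, and other group numbers, group sizes or contrasts would move the range.

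Missing a difference is a risk, not a certainty. The analysis is labelled additional; the prevalence estimate and the overall odds ratios do not depend on it. This is a desirable improvement rather than a flaw that threatens the study's main result.

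**What to change.** Delete the condition and replace the sentence with a commitment to:

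- report T2DM prevalence with 95% CI by ethnicity in all cases;
- test ethnicity-by-factor interaction terms in the full model for two or three prespecified factors (for example booking BMI, glucose at GDM diagnosis and family history), whatever the main effect of ethnicity;
- report ethnicity-specific odds ratios with 95% CIs beside the interaction p-value, labelled exploratory.

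The cost is one sentence of text and a little extra analysis, with no new data or participants. There are two drawbacks. Power will be low if the groups are small, so a non-significant interaction must not be read as evidence of no difference. A few more tests are also added: if independent, two or three tests at 0.05 give a chance of at least one false positive of 1 − 0.95² = 10% or 1 − 0.95³ = 14%. The exploratory label and the short list fixed in advance are meant to contain that.

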### **2.14 Ethical considerations**

This study will be performed in accordance with the principles with the Declaration of Helsinki (38).

The participants will be given advice on good food choices and physical activity at the conclusion of the study. They will also receive a "health card" with the results of all their anthropometric measurements and blood tests.

If any medical abnormalities (such as undiagnosed diabetes or hypertension) are identified during data collection the participants will be referred to their nearest day hospital for followup and management.

Permission to conduct the research will be sought from the Department of Health, the Groote Schuur, the Tygerberg Hospital and the Chris Hani Baragwanath Hospitals.

The study has received ethics clearance from the Human Research Ethics Committees of the University of Cape Town (Ref: 656/2015, Appendix 1) as well as permission to conduct research at the Groote Schuur Hospital (Appendix 2) in Cape Town.

The study will involve drawing blood samples from the forearms. Some of the potential risks in the blood collection include infection, delayed healing, bruising and some physical pain. The blood samples will be drawn using experienced nurses to minimize the risks.

All data will be de-identified during data capturing while the blood samples will be deidentified during aliquoting. The stored samples will not be used for any purpose other than the aims of the study. Any further use will only be carried out after ethical clearance from the UCT Human Research Ethics Committee.

All participants will go through the informed consent process which will involve an explanation of the study, the risks and benefits, the nature of their participation as well as their right to refuse to participate as well as stop their participation at any stage during or after the research.

The participants will receive a R100 to compensate for their travel expenses.

The lead investigators, the PhD student and the study coordinators are trained in good clinical practice (GCP). GCP principles will be adhered to during all stages of the conduct and reporting of the research.

